#### Usual care

Patients assigned to the usual care arm complete the same baseline interviews and follow-up as intervention patients. If requested by the admitting team or oncologist of record, usual care patients may also receive a palliative care consultation.

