### Analysis

We estimated our sample size based on one of our primary outcomes (time to palliative care) by utilizing data from the palliative care database on consultation in patients with advanced cancer. The baseline mean time to consultation for such patients seen by palliative care was 9 days (SD = 12). We estimated that our intervention would decrease this number by at least 50%, to 4.5 days (estimated SD = 6 days). Calculations employ two-tailed tests (α = 0.05, with β = 0.80). We plan to enroll and randomize at least 140 patients. We expect to have at least 80% power with α = 0.05 (two-sided) to detect clinically meaningful differences in these primary outcome variables with 70 subjects/group.

The primary analysis will be a traditional intention-to-treat that will compare intervention to control subjects on our predetermined primary and secondary outcomes. Two sample *t*-tests, Mann–Whitney, or *χ*^2^ will be used as appropriate depending on whether the outcome is continuous or discrete, and whether it is normally distributed. For the quality of life data, where there is a baseline score, ANCOVA will be used to compare outcomes between the two groups, and patients who die will be excluded from this analysis. A series of secondary analyses will be conducted if there is significant contamination between the intervention and control group. In the first of these sets of analyses, randomization assignment will serve as an instrumental variable and percentage of admissions receiving palliative care will be included as a covariate. We will also compare primary and secondary outcomes per protocol (i.e., patients will be grouped according to whether they received a consultation, rather than on their randomization scheme). We expect outliers in our outcome data and will not be excluding them from the analysis. Because of the small sample size, we will not account for permuted blocked randomization in the analyses.

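### The instrumental-variable analysis for contamination makes palliative care receipt a covariate and names no instrumented exposure; followed literally, it does not estimate the effect of consultation

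*Protocol article*

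**What the plan says.** The Analysis section of the protocol article makes intention-to-treat primary: "The primary analysis will be a traditional intention-to-treat that will compare intervention to control subjects on our predetermined primary and secondary outcomes". It then adds a contingency: "A series of secondary analyses will be conducted if there is significant contamination between the intervention and control group". The first of these secondary analyses is described in one clause: "randomization assignment will serve as an instrumental variable and percentage of admissions receiving palliative care will be included as a covariate". The second compares patients by treatment received: "patients will be grouped according to whether they received a consultation, rather than on their randomization scheme".

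Contamination is built into the design. Under Usual care, at the request of the admitting team or the oncologist, "usual care patients may also receive a palliative care consultation". The article gives no expected consultation rate for usual care.

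The Analysis section does not name the variable to be instrumented or the coefficient to be reported. It also does not say whether the percentage is measured per patient or per arm.

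**The concern.** An instrument is used because some exposure is endogenous. Here that exposure is receipt of a consultation, which in usual care depends on a clinician's request and so may follow the patient's prognosis. The clause names the instrument correctly but gives the exposure the role of an exogenous adjuster. An analyst who regresses the outcome on assignment and receipt together conditions on a post-randomisation variable. Neither coefficient from that model is then a contamination-corrected effect.

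The companion analysis groups patients by receipt and so gives up randomisation. That leaves the instrumental-variable step as the only randomisation-based answer to contamination in the plan. The Discussion intends the trial's effect estimates to inform a larger multicentre trial, so a wrong corrected effect could be carried into that design.

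**Working it through.** **1. The plan's own figure.** The same section gives "The baseline mean time to consultation for such patients seen by palliative care was 9 days (SD = 12" in controls, a reduction "to 4.5 days (estimated SD = 6 days" with intervention, and "Calculations employ two-tailed tests (α = 0.05, with β = 0.80", where 0.80 is read as power. With unequal variances, n per group = (12² + 6²)(1.960 + 0.842)² / 4.5² = 180 × 7.849 / 20.25 = 69.8, so 70. This reproduces the stated 70 per group. Power at 70 is 80.1% (normal) or 79.6% (t). It does not bear on the contamination analysis.

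**2. What the literal model estimates.** Let Z be assignment, D the patient's own receipt (0/1), Δ the difference between arms in the proportion consulted, and τ a constant true effect of consultation.

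- Intention-to-treat difference: ITT = τΔ.
- Instrumental-variable (Wald) estimate: ITT/Δ = τ.
- Literal model, outcome on Z and D: the receipt coefficient is bD = τ + B, where B is the within-arm covariance of D with the unmeasured part of the outcome, divided by the within-arm variance of D.
- Least squares gives ITT = bZ + bD·Δ, so the assignment coefficient is bZ = τΔ − (τ + B)Δ = −BΔ.

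The assignment coefficient does not contain τ at all. It is zero if receipt is unrelated to prognosis, and otherwise it measures only the confounding. The receipt coefficient equals τ only when B = 0.

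**3. Size, under assumptions.** The documents give neither receipt rates nor confounding strength, so these are assumed: 90% consulted in the intervention arm; p0 = 10%, 25% or 40% in usual care; receipt set by a latent threshold correlated g = 0, 0.3 or 0.6 with severity in both arms; severity lowers the outcome by 0.5 SD per SD (higher outcome is better). Then B = −0.5·g·(φ1 + φ0)/(p1q1 + p0q0), where p1 = 0.90, q = 1 − p and φ is the normal density at each arm's threshold.

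Example with p0 = 25% and g = 0.3: B = −0.15 × (0.1755 + 0.3178)/(0.09 + 0.1875) = −0.267, and Δ = 0.65, so bZ = 0.173. Simulation with 400,000 patients gave 0.172 when τ = 0 and 0.170 when τ = 0.5.

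| p0 | g | bZ (any τ) | bD if τ = 0 | bD if τ = 0.5 | Wald |
|---|---|---|---|---|---|
| any | 0 | 0 | 0 | 0.50 | τ |
| 10% | 0.3 | 0.23 | −0.29 | 0.21 | τ |
| 10% | 0.6 | 0.47 | −0.59 | −0.09 | τ |
| 25% | 0.3 | 0.17 | −0.27 | 0.23 | τ |
| 25% | 0.6 | 0.35 | −0.53 | −0.03 | τ |
| 40% | 0.3 | 0.13 | −0.26 | 0.24 | τ |
| 40% | 0.6 | 0.26 | −0.51 | −0.01 | τ |

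So with a true effect of zero, bZ runs from 0.13 to 0.47. Reversing the sign of the severity effect on the outcome mirrors it to −0.13 to −0.47. In the simulations two-stage least squares gave −0.01 to 0.00 when τ = 0 and 0.49 to 0.51 when τ = 0.5.

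**4. At the planned size.** In 3,000 simulated trials of 140 patients (90% against 25%, τ = 0.5), the receipt coefficient was negative in 15% at g = 0.3 and 56% at g = 0.6, against about 3% for two-stage least squares.

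**5. Arm-level percentage.** A per-arm percentage equals p0 + ΔZ, an exact linear function of Z. Entered beside assignment, it gives a design matrix of rank 2 with 3 columns, so the model is not estimable. Entered as the only regressor in place of Z, its slope is ITT/Δ, which is the Wald estimate exactly.

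**6. Per-patient share of admissions.** If the percentage is taken over each patient's own admissions, its denominator includes readmissions, which Table 3 lists as a secondary outcome.

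**The case against.** The strongest reply is that the clause does call assignment an instrument, and receipt is the only other variable it names. Covariate may then simply mean the regressor in the second stage. On that reading the analysis is valid two-stage least squares, and the literal model in step 2 is not what was meant. This stands as a possibility, and the document does not settle it. It does not remove the point, because the written role is the wrong one and both readings call for the same correction.

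A reader might infer that the plan will give a wrong-signed effect. The documents do not support that. With sicker patients consulted more often, a wrong-signed assignment coefficient requires severity and consultation to push the outcome in the same direction. The Discussion hypothesises benefit from consultation, while severity would be expected to do harm. With those opposing signs the assignment coefficient keeps the right sign, although it contains no information on the effect. The receipt coefficient crosses zero only at the strongest confounding tried, and then slightly.

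A reader might also infer that the model can never be fitted. That holds only when an arm-level percentage is entered beside assignment.

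It is also fair to say that an article may leave the full two-stage specification to another document. The point here is the role that the article does assign to receipt, not the missing detail.

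**Conclusion.** The instrumental-variable analysis is mis-stated, or at best ambiguous. Taken literally, it does not correct for contamination unless receipt is unrelated to prognosis. That receipt in usual care follows prognosis is plausible, because a clinician requests it, but it is assumed. The sizes in the table rest on assumed receipt rates and confounding, and which error appears depends on the coefficient reported.

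The impact is moderate. The analysis is secondary, runs only if contamination is judged significant, and sits in a pilot whose intention-to-treat analysis and sample size are untouched. Nothing here supports a claim that the primary results are compromised.

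**What to change.** Replace the clause with a statement of this kind: each patient's own receipt of a palliative care consultation (yes/no) is the endogenous exposure; randomised assignment is the only instrument; only baseline variables enter as covariates; estimation is by two-stage least squares or, without covariates, the Wald ratio (intention-to-treat difference divided by the difference in proportion consulted); and the result is reported as the complier average causal effect. Add that this analysis is not applied to rate or timing of consultation, because there the exposure is itself the outcome.

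The cost is a sentence or two of wording. No new data are needed, consultation is already abstracted from the medical record (Table 3), and Trial status says that the trial was still enrolling at submission.

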### Outcome measures

Outcomes were specified ahead of time, and include the rate and timing of palliative care consultation, quality of life and depression at 12 weeks, health care utilization, and survival. Independent variables are collected via a baseline interview with the patient or obtained from the electronic medical record, and are listed in Table 2. Dependent variables are listed in Table 3. The primary outcomes include rate and timing of palliative care consultation, quality of life and depression at 12 weeks, hospital length of stay, and survival. Secondary outcomes include costs during the index admission, ICU admission and ICU days, and ED revisits and re-hospitalization at 30 and 180 days. Objective outcomes were chosen that could be obtained from a chart or administrative data review to eliminate the possibility of recall bias or differential follow-up rates between the intervention and care-as-usual group.

**Table 2 T2:** Independent variables

**Variable**	**Measurement**	**Source**
Treatment group	Intervention, usual care	Research coordinator
Primary MD status	Full-time faculty/hospitalist, voluntary/private practice	Medical Record
Primary MD specialty	Heme/Onc, general medicine, other	Medical Record
Age	Years	Medical Record
Gender	Female, Male	Medical Record
Race/Ethnicity	Asian, Black, Hispanic Black, Hispanic White, Native American, White, Other	Patient Interview
Religion	Catholic, Protestant, Jewish, Muslim, Buddhist, Other, None	Patient Interview
Cancer diagnosis	Tumor type and stage	Medical Record
Performance status	ECOG Performance Status	Patient Interview
Medical comorbidities	Charlson co-morbidity index	Medical Record
Prior living situation	Home, nursing home, hospice	Patient Interview
Use of formal home care	Yes/no, Type of services, h/week	Patient Interview
Primary caregiver	Name and relationship/none	Patient Interview
Advance directives	Living will, health care proxy, power of attorney for health care/none	Patient Interview
Medical insurance	Medicare, Medicaid, Medicaid/Medicare managed care, Medicare managed care, traditional indemnity, self-pay, other	Administrative database, Medical Record

**Table 3 T3:** Dependent variables

**Variable**	**Measurement/Instrument**	**Source**

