**Primary Dependent Variables**		
Rate and timing of palliative care consultation	Yes/No; Days from enrollment to consultation	Medical Record
Quality of life	FACT-G at 12 weeks	Patient Interview
Depression	PHQ-9 at 12 weeks	Patient Interview
Hospital length of stay	Days during index admission	Medical Record
Survival	Days from enrollment	Medical Record

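### The contamination analysis labelled per protocol is an as-treated comparison: circular for the consultation outcomes and open to immortal-time bias for stay, costs and survival

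*Protocol article*

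**What the plan says.** The Analysis section of the protocol article puts intention-to-treat first: "The primary analysis will be a traditional intention-to-treat that will compare intervention to control subjects". It then adds a conditional layer: "A series of secondary analyses will be conducted if there is significant contamination between the intervention and control group". The first of these analyses uses randomised assignment as an instrumental variable. The second is the one at issue: "We will also compare primary and secondary outcomes per protocol", explained in a parenthesis as meaning that "patients will be grouped according to whether they received a consultation, rather than on their randomization scheme". No outcome is excepted.

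The outcomes covered are listed under Outcome measures: "The primary outcomes include rate and timing of palliative care consultation, quality of life and depression at 12 weeks, hospital length of stay, and survival". Table 3 defines timing as "Days from enrollment to consultation", length of stay as "Days during index admission", and survival as days counted from enrollment. Index-admission costs are secondary.

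Consultation is open to both arms. Under Intervention arm, assigned patients are seen on the day of referral or the day after. Under Usual care: "If requested by the admitting team or oncologist of record, usual care patients may also receive a palliative care consultation". The planning figure for time to consultation in patients seen by the palliative care service is a mean of 9 days, SD 12.

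**The concern.** A per-protocol analysis keeps patients in their randomised arm and restricts it to those who followed the assigned course. Moving patients between groups according to what they received is an as-treated analysis. Three consequences follow.

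- **Circularity.** The grouping variable is itself one of the primary outcomes.
- **Immortal time.** Stay and survival are counted from admission or enrollment, but the event that defines the group happens later. A usual-care patient who goes home or dies early cannot enter the consulted group.
- **Confounding by indication.** In usual care a clinician decides who is referred, so consulted and non-consulted controls may well differ in prognosis. The article does not say in which direction.

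The Discussion says that the trial's effect estimates are meant to inform a larger multicenter trial. An estimate carrying the per-protocol label is likely to be given more weight than an as-treated comparison deserves. The trigger makes this worse: the analysis runs only when many controls have been consulted, which is when the immortal-time bias is largest.

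**Working it through.** **1. The plan's own figure.** The sample size rests on time to consultation: 9 days (SD 12) against 4.5 days (SD 6), two-sided α = 0.05, 80% power. 

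n per group = (1.960 + 0.842)² × (12² + 6²) / 4.5² = 7.849 × 180 / 20.25 = 69.8, rounded up to 70. 

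The stated 70 per group is reproduced. It does not bear on this point, except that the outcome on which the trial was sized is one for which the regrouped comparison cannot be made.

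**2. Consultation outcomes (no assumptions needed).** Let C = 1 if a patient was consulted. The regrouped comparison of rate is P(C = 1 | C = 1) against P(C = 1 | C = 0), which is 100% against 0% in any dataset. Days to consultation are defined only where C = 1, so the timing comparison has no second group.

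**3. Length of stay, with no true effect of consultation.** Inputs:

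- From the article: time to consultation in usual care has mean 9 and SD 12 days. It is used here as a proxy, since it describes patients who were seen.
- Assumed, because the article gives no figure: lognormal stay with mean 8 and SD 8 days; lognormal consultation time, independent of stay; 90% of intervention patients consulted; consultation counted in the index admission only; equal arms; and a share of controls that is referable, varied from 10% to 70%.

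A control counts as consulted if referable and if the consultation time falls before discharge. Simulation gives the share f of controls consulted, and their mean stay if consulted (a) and if not (b). Pooling with the intervention arm, whose mean stay is 8.0 whether consulted or not:

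- consulted mean = (0.9 × 8.0 + f × a) / (0.9 + f)
- not-consulted mean = (0.1 × 8.0 + (1 − f) × b) / (0.1 + 1 − f)

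| Referable controls | f | a | b | Consulted | Not consulted | Spurious difference |
|---|---|---|---|---|---|---|
| 10% | 0.051 | 11.2 | 7.8 | 8.2 | 7.8 | +0.3 |
| 25% | 0.128 | 11.1 | 7.5 | 8.4 | 7.6 | +0.8 |
| 50% | 0.257 | 11.1 | 6.9 | 8.7 | 7.0 | +1.6 |
| 70% | 0.360 | 11.1 | 6.3 | 8.9 | 6.5 | +2.4 |

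Differences were taken before rounding. Worked line for 50%: (7.2 + 0.257 × 11.10) / 1.157 = 8.69; (0.8 + 0.743 × 6.92) / 0.843 = 7.05; difference 1.64. The randomised arms stay equal at 8.0 and 8.0.

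With 140 patients and a nominal 5% Mann–Whitney test, the as-treated comparison of stay rejects in about 11–14% of null trials at 25% referable, about a third at 50%, and about 60% at 70%. At 10% there is little inflation.

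**4. Survival, with no true effect.** With assumed median survival of 60 to 180 days and 25–50% of controls earmarked for referral, the as-treated hazard ratio is 0.96–0.99 if consultation is counted in the index admission, and 0.87–0.97 if it is counted over 180 days. Under randomised grouping it is 0.99–1.01. These figures contain immortal time only. Selective referral of patients with a worse prognosis would push the other way.

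**The case against.** The case on the other side has weight.

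- **Low standing.** Intention-to-treat is primary. The regrouping is secondary, conditional on contamination, and listed after an instrumental-variable analysis, in a pilot meant to give preliminary estimates. This stands, and it limits the severity.
- **The parenthesis discloses the grouping.** A careful reader sees how the groups are formed. This softens the labelling point but does not cure the circularity or the immortal time.
- **Detail left to a fuller document.** Landmark days and covariates may well be set out elsewhere. But the criticism is of a rule the article states, which applies the regrouping to every primary and secondary outcome.

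Three stronger readings are tempting, and the documents do not support them. First, a reader might infer that the bias would manufacture support for the intervention. For stay it does the opposite: consulted patients appear to stay longer, while the Discussion hypothesises lower utilization, so the bias could hide a real benefit. Second, a reader might infer that controls are referred because they are sicker. The Usual care section says only who may request a consultation. Third, a reader might take the 2.4-day figure as the expected size. It needs 70% of controls to be referable, and the article gives no contamination rate; at 10% the figure is about 0.3 days.

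**Conclusion.** The point holds at moderate severity. The wrong label, the 100% versus 0% comparison for consultation rate and the missing comparison group for timing follow from the article's text alone. So does the presence of immortal time for stay and survival, given the time origins in Table 3 and a grouping event that comes later; index-admission costs follow stay. The size does not follow from the text. Under the assumptions shown, the spurious excess in stay runs from about 0.3 to 2.4 days and grows with contamination. For survival the immortal-time part favours the consulted group, modestly at 25–50% of controls earmarked, but confounding by indication of unknown direction leaves the net direction open. Which outcome suffers more depends on whether consultation is counted in the index admission or over six months, which the article does not state. The intention-to-treat results are untouched.

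**What to change.** In the Analysis section:

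1. Call the regrouped comparison as-treated and exploratory, and state the window in which a consultation counts.
2. Omit it for rate and timing of consultation.
3. For survival and length of stay, enter consultation as a time-dependent exposure, or classify patients at a landmark day fixed in advance and analyse only what follows. Adjust for baseline ECOG status, Charlson index and tumour type, all listed in Table 2. Do not report an as-treated cost comparison without equivalent handling.
4. Rest the conclusion about contamination on the instrumental-variable analysis already planned, correctly specified: assignment is the instrument and each patient's receipt of consultation is the exposure.

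This needs no new baseline data, only changed wording and slightly more analysis. A landmark loses patients discharged or dead before the chosen day. The instrumental-variable estimate will be imprecise at about 70 per group. With a yes/no exposure it also assumes that assignment acts only through whether a consultation took place; earlier timing among patients consulted in either arm would strain that assumption, and the report should say so.

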## Discussion

Here, we describe the design of a clinical trial to determine the impact of a palliative care intervention for advanced cancer patients in the ED on quality of life, depression, health care utilization, and survival. While this is a pilot trial to establish feasibility, it will provide an estimate of the effect of the intervention on our predetermined outcomes that can be used to inform the design of a larger multicenter trial.

Systematic reviews of palliative care have concluded that trials are sparse and findings limited due to methodological shortcomings inherent to this patient population [11]. Only a small proportion of the research in palliative care is based on clinical trials [12], as recruitment and retention of these patients for palliative care studies have proven challenging [13]. The ED setting adds other unique challenges not encountered in other settings. The environment is crowded and chaotic, and there is little privacy. Patients often have a high symptom burden and are in significant distress, all of which can preclude participation in research. The specificity of our environment, coupled with the lack of published clinical trials in palliative care, make the publication of our study protocol especially important to further research in this arena.

Visits to the ED for patients with advanced cancer are common, demonstrating the potential for altering the clinical course of these patients in this setting [14,15]. Despite this, there has been almost no needs-based research in palliative care and emergency medicine, and until recently little emphasis has been placed on education, research, or practice guidelines in end-of-life or palliative care in this important setting [16]. While some EDs are pilot testing palliative care programs, there has not been a structured and rigorous approach to the development and testing of such interventions to assure their success and test their impact on predetermined outcomes.

We hypothesize that ED-initiated palliative care consultation will increase the rate and decrease time to palliative care consultation, improve quality of physical and mental health, decrease health care utilization, and may even increase survival. We believe that it is not only feasible to enroll ED patients with serious illness in trials of palliative care, but that the ED presents a unique window in which to do so.

